**Table 1 Tab1:** **Objectives of the Calcineurin Inhibitor-Sparing (CIS) trial**

Primary objective	To evaluate a CsA-based immunosuppressive regimen monitored by residual NFAT-regulated gene expression concerning reduction in cardiovascular risk assessed by the change in pulse wave velocity from baseline to six-month follow-up, compared to a CsA-based regimen monitored by CsA trough levels in renal allograft recipients
Secondary efficacy objectives	To evaluate, in treatment group:
	- a composite endpoint of biopsy-proven acute rejection (BPAR), graft loss, death and loss to follow-up at Month 6
	- Incidence of BPAR, graft loss, loss to follow-up or death at Month 6
	- S-creatinine and cystatin C at Month 6.
	- Renal allograft function (eGFR calculated by MDRD, Nankivell and Cockroft-Gault formulae) at Month 6
	- Evolution of renal function (S-creatinine) over time by slope analysis
	- Creatinine slope (1/serum creatinine versus time) including the treatment period between baseline and Month 6
Secondary safety objectives	To evaluate, in treatment group:
	- Incidence and severity of adverse events (AEs) and serious adverse events (SAEs)
	- Incidence of AEs leading to discontinuation from the study
	- Incidence of major cardiovascular events (myocardial infarction, apoplexy, peripheral arterial occlusive disease)
	- Pulse wave velocity, aortic pulse pressure, aortic systolic pressure, aortic augmentation index, ejection duration, heart rate variability
	- Changes in blood pressure (central and peripheral pulse pressure, systolic and diastolic, mean arterial blood pressure)
	- Changes in antihypertensive medication (number of antihypertensives)
	- Changes in lipids (cholesterol, LDL-, HDL-cholesterol, triglyceride) and lipid-lowering drugs
	- Changes in glucose levels, HbA1c and antidiabetic therapy
	- Changes in cardiovascular risk (for example Framingham score)
	- Changes in CsA-induced side effects (for example hypertrichosis, gingival overgrowth)
	- Incidence and severity of infections
	- Incidence and severity of malignancies
	- Changes in the quality of life assessed by the ESRD SCL™ questionnaire and SF12 questionnaire
Exploratory objectives	To explore the incidence of DSA in treatment group, and in relation to acute rejection, in a subset of patients at participating centres

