### Patient selection, randomisation and study treatment

All renal allograft recipients of the outpatient clinic of the Department of Nephrology, University Hospital Heidelberg, Germany, will be screened according to inclusion and exclusion criteria. Patients will be enrolled consecutively. After informed consent has been signed, the patient participates in the study. Each patient is uniquely identified by a patient number. The investigator dispenses the patient numbers in chronological order.

Patients are randomised after providing written informed consent in a 1:1 ratio by a web-based randomisation tool using block randomisation with fixed block lengths (Randomisation In Treatment Arms (RITA) randomisation system (University of Lübeck, Germany)). In patients assigned to the standard group (control group), CsA is administered adapted to CsA C0s of 80 to 150 μg/L. In patients assigned to the investigational group (NFAT group), CsA is administered adapted to residual NFAT-regulated gene expression of 15 to 30%. For safety reasons, CsA C0 should be ≥30 μg/L in all patients.

Patients should stay within the target trough blood levels or residual NFAT-regulated gene expression throughout the study. The adaption of CsA dosage starts after randomization as soon as the results of CsA C0 (control group) or NFAT-regulated gene expression (NFAT group) are available, and at subsequent visits, if necessary. Dose adjustments are performed in the control group if CsA whole blood levels are outside the target range of CsA C0 80 to 150 g/L and in the NFAT group if NFAT-regulated gene expression is outside the range of 15 to 30% at the time of study visits (baseline, Month 1, Month 3 and Month 6). Adaption of CsA dose will be performed according to the regular clinical practice in approximately 20% steps. In the case of severe CNI toxicity, dose reductions below the target levels may be performed at the investigators’ discretion. If CsA is interrupted for safety-related considerations for more than four consecutive weeks or more than two episodes longer than two weeks, the patient should be withdrawn from the study.

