### Statistical analysis

Statistical analyses will be performed by an independent statistician. The aim of the study is to prove that the CsA therapy monitored by residual NFAT-regulated gene expression is superior to CsA therapy monitored by CsA C0s, by testing the following hypotheses: the null hypothesis is that the change in PWV between baseline and Month 6 is the same in both treatment arms. The alternative hypothesis is that the change in PWV between baseline and Month 6 is lower or higher in the NFAT group than in the control group.

Analysis of covariance (ANCOVA) will be applied with treatment, age, baseline PWV and eGFR as covariates. The primary analysis will be performed on the intention-to-treat (ITT) population. The treatment groups will be compared, using least-square means derived from the ANCOVA model. The two-sided significance level is given by 0.05. Using an ANCOVA model instead of the two-sided unpaired *t* test, which was used for sample size calculation, increases the strength of the study, as the adjustment for covariates leads to a reduction in variance.

Missing values will be replaced by the ‘last observation carried forward’ (LOCF) approach. All secondary variables will be analysed in an exploratory way. Event rates will be estimated using the Kaplan-Meier method to handle patients who discontinue the treatment prior to suffering sufficiently from an event. The two groups will be compared using the log-rank test. This procedure will be applied for the BPAR, graft loss, death, as well as the composite endpoint of treatment failure. The main analysis will be performed at the last patient’s last visit at Month 6. No interim analyses or design adaptations are planned.

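### Patients with a long safety-related CsA interruption leave the study, not only the treatment, so their Month 6 outcomes are probably not collected although the primary analysis is ITT

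*Protocol article*

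**What the plan says.** The rule stands in the protocol article under Patient selection, randomisation and study treatment. Its trigger is narrow: "If CsA is interrupted for safety-related considerations". Its threshold and consequence follow directly: "for more than four consecutive weeks or more than two episodes longer than two weeks, the patient should be withdrawn from the study". What ends is study participation, not only study treatment. The article does not say that assessments continue afterwards.

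The Statistical analysis section then says of the primary comparison: "The primary analysis will be performed on the intention-to-treat (ITT) population". On gaps in the data it says: "Missing values will be replaced by the ‘last observation carried forward’ (LOCF) approach".

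For clinical events, the same section gives this reason for the method: "Event rates will be estimated using the Kaplan-Meier method to handle patients who discontinue the treatment prior to suffering sufficiently from an event". On its scope it adds: "This procedure will be applied for the BPAR, graft loss, death, as well as the composite endpoint of treatment failure". It also sets the status of these analyses: "All secondary variables will be analysed in an exploratory way".

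Table 1 lists as a secondary efficacy objective "a composite endpoint of biopsy-proven acute rejection (BPAR), graft loss, death and loss to follow-up at Month 6". The Outcome measures text describes the composite without loss to follow-up.

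**The concern.** Stopping a treatment and leaving a trial are different events, and the rule merges them. An ITT comparison needs the Month 6 outcome of each randomised patient, whatever happened to the treatment. Here the plan itself makes that outcome missing in a group defined by what happened on treatment, and then fills the gap with an earlier value. The patient stays in the ITT set, but the outcome does not.

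The reason for leaving is not neutral. The arms differ precisely in how CsA is dosed, so interruptions for toxicity may differ in number and kind between them. The Background links insufficient immunosuppression to a higher risk of rejection, and the abstract commits the trial to keeping immunosuppression sufficient. Patients who have been off CsA for weeks are therefore ones in whom later rejection should be seen and counted.

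**Working it through.** **1. The plan's own figure.** Inputs from Sample size calculation: difference 1.2 m/s, SD 1.5 (its unit is printed as ml/min; taken here as m/s), two-sided alpha 0.05, power 80%, unpaired t test. Exact power from the noncentral t distribution is 0.791 with 25 per group and 0.807 with 26, so 26 is the smallest sufficient number. With 5% drop-out, 52 / 0.95 = 54.7, rounded up to 55. Both stated figures reproduce.

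**2. How many patients.** The article gives no rate for interruptions beyond the threshold. The only related figure is the overall drop-out allowance: 0.05 × 55 = 2.75, about 3 patients for all reasons together. Any higher rate below is an assumption.

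**3. Precision if Month 6 PWV is missing and only observed cases are used** (t test, same difference and SD):

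| Missing of 55 | Patients per group | Power |
|---|---|---|
| 3 | 26 / 26 | 0.81 |
| 5 | 25 / 25 | 0.79 |
| 8 | 23 / 24 | 0.77 |
| 11 | 22 / 22 | 0.74 |

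**4. Bias under LOCF, NFAT arm.** Assume that a share f of this arm leaves before Month 3, so that baseline is carried forward and the change is 0, and that their true Month 6 change would have been the planned 1.2 m/s. The estimated difference is 1.2 × (1 − f). With 27 and 28 patients and SD 1.5:

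| f (assumed) | Difference, m/s | Power |
|---|---|---|
| 0 | 1.20 | 0.83 |
| 5% | 1.14 | 0.79 |
| 10% | 1.08 | 0.75 |
| 20% | 0.96 | 0.64 |

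These are unfavourable cases. Someone who leaves after Month 3 carries forward the Month 3 value, which may already contain part of the change.

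**5. Bias under LOCF, control arm.** The plan expects a change close to 0 here, so for a patient whose PWV stays flat LOCF does almost no harm. Selection of the primary endpoint, however, reports lower PWV on a CNI-free regimen than on CsA. Suppose 10% of controls leave and, off CsA, their PWV would truly have fallen by 1.2 m/s (both figures assumed). The control mean would fall by 0.10 × 1.2 = 0.12 m/s and the true difference as randomised would be 1.20 − 0.12 = 1.08 m/s. LOCF from baseline would report 1.20, an error in favour of the NFAT arm. Steps 4 and 5 point in opposite directions, so the sign of the bias cannot be fixed in advance.

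**6. Rejection, if follow-up ends at withdrawal.** Assume 10% of an arm leave early, with a 6-month risk of biopsy-proven rejection of 3% in those who stay and 10% to 30% in those who leave. The true risk is 0.9 × 0.03 + 0.1 × 0.10 = 3.7%, up to 0.9 × 0.03 + 0.1 × 0.30 = 5.7%. A curve that censors the leavers early shows about 3%. In an arm of 27 the shortfall is 27 × 0.007 = 0.2 to 27 × 0.027 = 0.7 expected events.

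**The case against.** The best case against runs as follows. The article condenses protocol version 1.2, and follow-up after withdrawal and the censoring date are the kind of detail left to that document or to an SAP. The rule has a narrow trigger: shorter interruptions, and dose reductions for severe toxicity, do not lead to withdrawal. Few patients will meet it. If CsA toxicity drives interruption, it would be expected more in the control arm, where the planned change is near 0 and LOCF dilutes nothing. The event analyses are exploratory, and the Discussion defers hard endpoints to later multi-centre trials.

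Much of this stands, and it limits the size of the point. It does not remove it. The withdrawal instruction is stated, not left out, and no SAP can analyse values that were never collected. The remark about the control arm holds only if PWV stays flat after CsA is stopped, which the investigators' own cited comparison makes doubtful.

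Three stronger readings are tempting and are not supported. A reader might infer that data are discarded; nothing says so, and withdrawn patients remain in the ITT set through LOCF, so the defect is data not collected. A reader might infer that events are censored when treatment stops; the Kaplan-Meier sentence suggests it but gives no censoring date. Table 1 might even count some of these patients as failures through loss to follow-up, though the Outcome measures text omits that component and it would not register a rejection as such. Lastly, a reader might conclude that the primary analysis is not ITT at all; for the large majority, who are followed to Month 6, it is.

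**Conclusion.** The point holds in this limited form. The withdrawal rule and the ITT primary analysis do not fit together: in patients beyond the interruption threshold, Month 6 PWV is on a plain reading not observed and is imputed for a reason tied to treatment and possibly to arm. Later rejection, graft loss or death in the same patients is likely to go unrecorded.

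The effect is probably small. At the planned 5% loss, about 3 patients are involved and power on observed cases stays at 0.81. Under assumed withdrawal of 10% in a single arm, the PWV difference would be wrong by about 0.12 m/s in either direction, depending on the arm. These magnitudes rest on assumed rates and assumed Month 6 values, since the article gives neither. The conflict between the passages does not depend on them. The planned sample size is correct as calculated. The consequence for events concerns exploratory analyses, but it touches the trial's own safety question.

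**What to change.** Leave the clinical criterion for CsA interruption unchanged and alter only its consequence for data collection. In Patient selection, randomisation and study treatment, replace withdrawal from the study by wording such as: recorded as off study treatment and followed to Month 6. Keep the scheduled PWV, creatinine and event assessments unless the patient withdraws consent.

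In Statistical analysis, state that PWV observed after treatment has stopped enters the ITT analysis, so that LOCF is not used where a Month 6 value exists. State also that events count up to Month 6 or last contact, regardless of treatment discontinuation. Reconcile the composite between Table 1 and Outcome measures, so that it is clear whether loss to follow-up is a failure.

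The cost is a short amendment, which would need review by the authority and ethics committee because recruitment had already opened, and a few additional follow-up visits. The visits are already in Table 2 and the patients come from the trial's own outpatient clinic.

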### Concomitant immunosuppression

The immunosuppressive regimen used in the study is widely accepted in clinical practice. All patients receive CsA and MPA therapy, with or without steroids. MPA is administered in a standard dosage of enteric-coated mycophenolate sodium (EC-MPS) (Myfortic™) 180 to 720 mg twice a day (BID) or mycophenolate mofetil (MMF) (Cellcept™) 250 to 1,000 mg BID. MPA exposure will be monitored if daily EC-MPS dose is below 720 mg/d or if MMF dose is below 1,000 mg/d. In this case, PK monitoring of EC-MPS will include MPA C0, C1, C2, C3, C4 and C6; and MPA-area under the curve (AUC) will be calculated according to Sommerer *et al.*
[36]. PK monitoring of MMF will include MPA C0, C0.5 and C2; and MPA-AUC will be calculated according to the Fixed-Dose Concentration-Controlled (FDCC) study
[37]. Target MPA-AUC for both drugs is 45 mg^*^h/L with a minimum of 30 mg^*^h/L.

Corticosteroids are administered according to local centre practice.

### Roles and responsibilities

The CIS study was designed by a steering committee consisting of nephrologists specialised in renal transplantation, an immunologist and a statistician. The CIS study is an investigator-initiated trial; the study sponsor is the Renal Clinic Heidelberg, Germany (Department of Nephrology, University Hospital Heidelberg, Germany). Regulatory study approval is provided by the competent authority, the ‘German Regulatory Authority’ as well as by the local Ethics Committee. The study is conducted by the investigators and the local Study Centre at the Department of Nephrology, University Hospital Heidelberg. Data management and biometry will be provided by the Institute of Medical Biometry and Informatics, University Heidelberg, Germany. Pharmacovigilance and monitoring will be performed by representatives of the independent Clinical Study Centre, University Heidelberg, Germany.

### Ethical, regulatory and management considerations

The study protocol (version 1.2, 23 December 2013) has received ethical and governance approvals by the German Regulatory Authority (reference number 4038718) as well as by the local Ethics Committee (Ethics Committee, University Hospital Heidelberg, Germany; reference number AFmo-622/2012). The CIS study was registered in the European Union Drug Regulating Authorities Clinical Trials (EudraCT) database on 18 July 2011 (EudraCT Identifier 2011-003547-21). The study protocol follows the principles of good clinical practice (GCP) and the study is performed in compliance with the Declaration of Helsinki. Researchers collecting data will have appropriate research permissions, where required. Written informed consent will be taken from each participant prior to study enrolment by an experienced investigator. All data will be managed and stored with protection of data privacy.

Documentation as well as corrections, if necessary, will be done in accordance with GCP guidelines. All protocol-required information collected during the trial must be entered in the case report form (CRF). The completed CRFs will be sent to the Institute of Medical Biometry and Informatics, University Heidelberg, Germany. Data assessment will be performed twice by two independent persons to avoid incorrect entries. The completeness, validity and plausibility of data are examined by validating programs, which thereby generate queries. The investigator or the designated representatives are obliged to clarify or explain the queries. All changes from the original data are documented on audit files. Data will be maintained using the statistical SAS program, Version 9.0 or higher (SAS Institute Inc., Cary, NC, USA). Monitoring will be performed regularly by the independent Clinical Study Centre, University Hospital Heidelberg, to check the completeness of the contents of records and the CRFs, the adherence to the protocol and to GCP, the progress of enrolment, and to ensure that study drug is being stored, dispensed, and accounted for according to specifications. Patient insurance for compensation to those who suffer harm from trial participation is provided.

### Sample size calculation

The changes for PWV between baseline (Visit 1) and six-month follow-up (Visit 3) are calculated and compared between the groups. For the CsA standard group, the estimated change in PWV is close to 0. It is further assumed that the baseline values are similar for both groups. From study reports by Bahous *et al.*
[29] and Seckinger *et al.*
[30], the probable change from baseline to the six-month follow-up in the CsA low-dose group is estimated as δ = 1.3 m/s. Since some patients are expected to reveal treatment complications that might decrease the differences between the two treatment groups, the expected absolute effect considered for sample size calculation is δ = 1.2. The standard deviation is assumed to be σ = 1.5 ml/min. Similar standard deviations have been reported by Seckinger *et al*.
[30] and Bahous *et al.*
[29], in different comparison scenarios. However, as the absolute effect was conservatively estimated, the proposed assumptions are likely to yield a sample size that is large enough. With α = 0.05 and 1-β = 80%, n = 26 patients per group are required to demonstrate superior efficacy of the NFAT group compared to the CsA standard group in PWV when using a two-sided unpaired *t* test. Including a small drop-out rate of 5%, this results in a total number of 55 patients.

### Statistical analysis

Statistical analyses will be performed by an independent statistician. The aim of the study is to prove that the CsA therapy monitored by residual NFAT-regulated gene expression is superior to CsA therapy monitored by CsA C0s, by testing the following hypotheses: the null hypothesis is that the change in PWV between baseline and Month 6 is the same in both treatment arms. The alternative hypothesis is that the change in PWV between baseline and Month 6 is lower or higher in the NFAT group than in the control group.

Analysis of covariance (ANCOVA) will be applied with treatment, age, baseline PWV and eGFR as covariates. The primary analysis will be performed on the intention-to-treat (ITT) population. The treatment groups will be compared, using least-square means derived from the ANCOVA model. The two-sided significance level is given by 0.05. Using an ANCOVA model instead of the two-sided unpaired *t* test, which was used for sample size calculation, increases the strength of the study, as the adjustment for covariates leads to a reduction in variance.

Missing values will be replaced by the ‘last observation carried forward’ (LOCF) approach. All secondary variables will be analysed in an exploratory way. Event rates will be estimated using the Kaplan-Meier method to handle patients who discontinue the treatment prior to suffering sufficiently from an event. The two groups will be compared using the log-rank test. This procedure will be applied for the BPAR, graft loss, death, as well as the composite endpoint of treatment failure. The main analysis will be performed at the last patient’s last visit at Month 6. No interim analyses or design adaptations are planned.

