## Methods/Design

### Study design

The CIS trial (RCHD-1004, protocol version 1.2, 23 December 2013) is a prospective, randomised, parallel-grouped, confirmatory study (Figure 
1). This trial is a single-centre study performed at the Renal Clinic Heidelberg (Department of Nephrology, University Hospital Heidelberg). Stable renal allograft recipients on CsA treatment are randomised, to be monitored and adapted either by CsA C0s or residual expression of NFAT-regulated genes. The study period is six months.

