### Outcome measures

The change in the arterial stiffness assessed by PWV from baseline (Visit 1) to Month 6 (Visit 3) is the primary efficacy objective of the study. Carotid-femoral PWV pressure as well as central blood pressure will be assessed using a validated SphygmoCor device from AtCor Medical, Sydney, Australia. The assessment of PWV is performed blinded to drug treatment, results of CsA C0 or residual NFAT-regulated gene expression. Measurement of PWV as well as peripheral and central blood pressure is performed at randomisation (Visit 1), Month 3 (Visit 3), and Month 6 (Visit 4).

Secondary efficacy and safety objectives are given in Table 
1. One secondary objective of the CIS trial is to evaluate the two treatment groups with respect to a composite efficacy failure endpoint comprising biopsy-proven acute rejection (BPAR), graft loss or death at the end of the study, consistent with recommendations by the European Medicines Agency (EMEA)
[31]. Additional secondary objectives include individual components of this composite failure endpoint.

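### LOCF as the primary missing-data rule puts a Month 3 or baseline PWV in place of a missing Month 6 value: little bias at the planned 5% drop-out, more if missingness is higher or unequal

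*Protocol article*

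**What the plan says.** The Statistical analysis section sets the primary model, "Analysis of covariance (ANCOVA) will be applied with treatment, age, baseline PWV and eGFR as covariates", and the population, "The primary analysis will be performed on the intention-to-treat (ITT) population". It then gives one rule for incomplete data: "Missing values will be replaced by the ‘last observation carried forward’ (LOCF) approach". The next sentence turns to the secondary variables, so the rule applies to the primary endpoint at least. The hypothesis in the same section concerns the change from baseline to Month 6.

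Under Outcome measures, PWV measurement "is performed at randomisation (Visit 1), Month 3 (Visit 3), and Month 6 (Visit 4". Table 2 agrees and shows no PWV at Month 1. (The first sentence of Outcome measures and the Sample size calculation call the six-month visit Visit 3. I follow Table 2, where Month 6 is Visit 4.)

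On dosing, "Adaption of CsA dose will be performed according to the regular clinical practice in approximately 20% steps". Table 2 marks CsA adaption at baseline, Month 1 and Month 3.

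The Sample size calculation states: "For the CsA standard group, the estimated change in PWV is close to 0". It assumes a difference of 1.2 m/s, an SD of 1.5 (unit printed as ml/min, read here as m/s) and 5% drop-out.

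**The concern.** With three PWV measurements, carrying forward can do only two things. A patient who has Month 3 but not Month 6 keeps the Month 3 value. That value was taken before any adaption made at the Month 3 visit could act. A patient with no PWV after baseline gets a change of 0, if baseline counts as an observation that can be carried.

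Under the plan's assumptions a zero is about right for a control patient and wrong for an NFAT patient who would have improved. The estimate becomes a mixture of Month 6, Month 3 and no-change values, whereas the hypothesis is about Month 6. The filled-in values also count as real observations, so the standard error does not grow when data are lost.

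Missingness may be related to treatment. The protocol withdraws patients after prolonged CsA interruption, and the sample size text expects complications in some patients. At stake are the size of the reported effect and the width of its interval.

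**Working it through.** **The plan's own figure.** The standardised effect is 1.2/1.5 = 0.8. A two-sided t test at 0.05 with 80% power needs 25.5 per group, rounded up to 26 (power 80.7%). Then 52/0.95 = 54.7, which gives 55. The stated sample size is reproduced and does not depend on the missing-data rule. Five per cent of 55 is 2.75, about 3 patients.

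**Expected LOCF estimate.** Let d be the share of NFAT patients without a Month 6 PWV, s the share of those with baseline only, and f the fraction of the effect present at Month 3. With zero change in controls, and drop-outs who would have kept the effect:

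expected difference = 1.2 × [(1 − d) + d × (1 − s) × f]

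The documents give none of d by arm, s or f, so a range is shown. With f = 0.5 (m/s):

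| d | s = 0 | s = 0.5 | s = 1 |
|---|---|---|---|
| 5% | 1.170 | 1.155 | 1.140 |
| 10% | 1.14 | 1.11 | 1.08 |
| 20% | 1.08 | 1.02 | 0.96 |

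Example: 1.2 × (0.95 + 0.05 × 0.5 × 0.5) = 1.2 × 0.9625 = 1.155. If f = 1 and s = 0 there is no bias (1.20). If f = 0, every column equals the last one.

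**Standard error and power.** These come from a simulation with 27 patients per arm, 5,000 runs per scenario, SD of change 1.5, Month 3/Month 6 correlation 0.5, baseline PWV as the only covariate, missingness completely at random, and s = f = 0.5. The comparator is ANCOVA on observed Month 6 values.

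| Missing, control/NFAT | LOCF estimate (SE) | Observed-only estimate (SE) | Power, LOCF / observed |
|---|---|---|---|
| 5%/5% | 1.153 (0.407) | 1.200 (0.421) | 78.8% / 79.2% |
| 10%/10% | 1.108 (0.403) | 1.198 (0.433) | 76.4% / 76.9% |
| 20%/20% | 1.019 (0.397) | 1.198 (0.463) | 70.9% / 71.4% |
| 5%/15% | 1.066 (0.405) | 1.199 (0.434) | 72.2% / 76.5% |

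With complete data the SE is about 0.41 and power 81 to 82%. The ratio of the LOCF SE to the observed-data SE is 0.407/0.421 = 0.967 at 5% missing, 0.403/0.433 = 0.931 at 10% and 0.397/0.463 = 0.857 at 20%. It is thus about 3%, 7% and 14% smaller.

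**Coverage.** At 5% missing the bias is 0.045/0.407 = 0.11 SE, and 95% intervals cover the Month 6 effect about 95% of the time. At 20% missing with s = 0.5 it is 0.18/0.397 = 0.45 SE and coverage is about 93%. At 20% with s = 1 it is 0.24/0.378 = 0.63 SE and coverage is about 90%.

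**Type I error.** With no effect and no drift, 20% missing in both arms gave 5.0% (s = 1) and 5.3% (s = 0.5). The direction can change. Suppose there is no effect, both arms drift by +0.5 m/s, and 20% are missing in the NFAT arm only, all with baseline only. Then LOCF gives 0.2 × (0 − 0.5) = −0.10 m/s, a spurious benefit for NFAT monitoring, with 5.9% rejection (4.8% on observed values).

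**The case against.** - **The effect is small as planned.** At 5% drop-out the bias is 0.03 to 0.06 m/s (f = 0.5) against an SE of about 0.41, and it points toward no difference. The plan already cut its effect from 1.3 to 1.2 for complications, a margin of about 8%, against about 4% attenuation here. This stands, and it sets the severity. That cut concerns the size of the expected effect, however, and does not justify the imputation rule.
- **The benchmark assumes that drop-outs keep the benefit.** If withdrawn NFAT patients have none at Month 6, the ITT effect at 10% missing is 1.2 × 0.9 = 1.08. LOCF then gives 1.11 and the observed-data analysis 1.20, so LOCF is closer. This stands. A missing-at-random model shares the weakness, which is why the fix includes a sensitivity analysis for this case.
- **The SE claim is relative.** The LOCF model SE nearly matches that estimator's own simulated spread (0.407 against 0.412 at 5% missing). It is too small only as a measure of what the observed Month 6 data can say about Month 6. With equal missingness, power is almost the same as for observed values alone.
- **The article does not say whether baseline is carried.** If it is not, the s = 0 column applies and the bias at 5% is 0.03 m/s.

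A reader might also infer two stronger points that the documents do not support. The first is that Month 3 PWV reflects a dose only part-way through adjustment. The protocol adapts the dose from baseline and later only where needed, so a patient may be in range by Month 3. The second is that LOCF hides graft failure in the creatinine and eGFR comparisons. Nothing says that those values are missing after graft loss and then carried forward. Graft loss is its own endpoint and part of the composite, analysed by Kaplan-Meier and log-rank, and the secondary variables are exploratory.

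**Conclusion.** The point holds as a minor one. LOCF is fixed for the primary endpoint, and with this visit schedule it does not in general estimate the Month 6 difference that the hypothesis names. With s = f = 0.5 and drop-outs who would have kept the effect, the expected estimate is 1.15 to 1.16 m/s at the planned 5% missing, 1.11 at 10% and 1.02 at 20%, against 1.20. The SE is about 3%, 7% and 14% smaller than observed Month 6 data support.

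A reader might conclude that the primary test is invalid. The calculations do not show that: type I error stays near 5% without drift, and coverage is nearly nominal at planned drop-out. The larger distortions need missingness that is higher or unequal between arms, or a common drift. The documents predict none of these, but the plan does not protect against them either.

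**What to change.** Make the primary analysis a mixed model for repeated measures on PWV change at Months 3 and 6. Include treatment, visit, treatment-by-visit, age, baseline PWV by visit and eGFR, with unstructured covariance, and take the Month 6 treatment contrast as the primary estimate. Without missing data this gives essentially the planned ANCOVA contrast. Keep LOCF as a sensitivity analysis and state whether baseline values are carried. Add a sensitivity analysis in which withdrawn NFAT patients are assumed to lose the benefit, for example by imputing their Month 6 change from the control arm.

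The cost is analysis-plan wording and a few lines of SAS. Month 3 PWV is already collected and the sample size of 55 is unchanged. The downside is reliance on missing-at-random. Patients with baseline PWV only add no outcome data to the model, so report their number by arm. The mixed model itself was not simulated here; the comparator above was ANCOVA on observed Month 6 values.
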